### Intervention

#### Specialised orthotic care

Patients in the intervention group will receive specialised orthotic care at an expert centre that has implemented the Dutch guideline for leg orthoses^18^ and has facilities for 3D gait analysis, gait training and fabricating custom-made leg orthoses. For the orthotic care process, protocols of the guideline will be used and treatment integrity checks will be performed to ensure compliance with the guideline.

First, the health problems and goals of the patient will assessed by means of an interview, questionnaires, physical examination and 3D gait analysis. Based on these assessments, the multidisciplinary care team will identify how the patients’ problems and goals are best matched to an orthotic solution. The desired level of functioning for the patient and the required orthotic functions will be described in a care plan. Accordingly, the orthosis will be custom fabricated by an orthotic technician. After delivery of the orthosis, instructions on use and maintenance will be given to the patient and, when indicated, the patient receives gait training supervised by an experienced physiotherapist. Finally, after 3 months of using the orthosis, experiences of the patient as well as the desired level of functioning and orthotic functions will be evaluated. When needed, the orthosis will be adjusted based on the evaluation. The provision process will be extensively documented for each participant individually by an investigator who is not blinded.

#### Usual orthotic care

Participants in the control group will receive usual orthotic care from a rehabilitation physician at their regular care centre. Treatment can vary across centres and may include provision of orthopaedic shoes, provision of off-the-shelf or custom-made AFOs or provision of off-the-shelf or custom-made KAFOs according to the discretion of the practitioners and local policy of the centre. For participants who already use an orthosis at baseline, usual orthotic care will concern the provision of a new orthosis which may be identical of different from the orthosis being used. The provision process in the usual care centres will be extensively documented for each participant individually by an investigator who is not blinded.

### Outcome measures

Relevant demographic variables, anthropometrics and clinical characteristics will be measured at baseline (T1). Clinical characteristics to be evaluated include: (1) manually assessed muscle strength of the left and right hip flexors and extensors, hip abductors and adductors, knee flexors and extensors, ankle plantar and dorsal flexors and ankle invertors and evertors, scored according to the MRC scale and (2) passive range of motion of the hip, knee and ankle joints (left and right). Furthermore, (3) occurrence of joint deformities and (4) impairments in sensory function will be evaluated.

Primary outcomes and secondary outcomes (described below) will be assessed at baseline (T1) and at 3 and 6 months after orthotic treatment (T2 and T3, respectively). Additionally, orthotic properties (such as type, weight, material and orthotic functions) and adverse events due to the use of the device (such as pressure sores, pain, muscle soreness) will be documented. The use of any medication during the study will be monitored at all measurement time points and documented in the cost questionnaires. All collected outcomes will be entered into a Castor database. An overview of all outcomes per measurement visit is given in table 1.

**Table 1 T1:** Overview of outcomes per measurement session

		Baseline	Follow-up	
		T1 measurement (screening)	T2 measurement (12 weeks after delivery)	T3 measurement (24 weeks after delivery)
**Primary outcomes**				
Walking energy cost	6 MWT	X	X	X
Personal goals	GAS	*Setting goals*	*X*	*X*
**Secondary outcomes**			* *	* *
Walking speed	6 MWT	*X*	*X*	*X*
Gait biomechanics	3DGA	*X**	*X*	*X*
Stability	NRS	*X*	*X*	*X*
Physical functioning	SF36-PF	*X*	*X*	*X*
Fear of falling	FES	X	X	X
Fall rate	Questionnaire	X	X	X
Fatigue	FSS	X	X	X
Satisfaction	D-Quest	X†	X	X
**Additional outcomes**				
Demographics	Intake	X		
Anthropometrics	Physical exam	X		
Muscle strength	Physical exam	X		
Joint passive range of motion	Physical exam	X		
Sensory function	Physical exam	X		
Orthotic properties	CRF	X†	X	X
Adverse events	CRF		X	X
**Economic evaluation**				
Resource use‡	Cost questionnaire	X	X	X
Health-related quality of life‡	EQ-5D-5L	X	X	X

*Gait analysis conditions at baseline that will be used for statistical analysis concern walking with shoes only or walking with the old orthosis (in case a participant uses an orthosis at baseline).

†Outcomes will only be assessed in case a participant uses an orthosis at baseline.

‡Outcomes for the economic evaluation will also be assessed directly after delivery of the orthosis.

CRF, clinical report form; 3DGA, 3-dimensional gait analysis; D-Quest, Dutch version of the Quebec User Evaluation of Satisfaction with Assistive Technology; EQ-5D-5L, 5-Level version of EuroQol 5D; FES, Falls Efficacy Scale; FSS, Fatigue Severity Scale; GAS, Goal Attainment Scale; 6MWT, 6-minute walk test; NRS, Numeric Rating Scale; SF36-PF, Physical Functioning Scale of the Short-Form Health Survey.

#### Primary outcomes

Primary outcomes are walking energy cost and the achievement of personal treatment goals. Walking energy cost will be determined during a 6-minute walk test (6MWT) in which participants walk at a self-selected comfortable speed on an indoor oval track in their preferred walking direction (which will be kept similar over measurement time points). Simultaneously, oxygen uptake (VO_2_) and the respiratory exchange ratio (RER) will be measured breath by breath with the Cosmed K5 portable gas analysis system (Cosmed, Rome, Italy). Mean VO_2_, RER and walking speed values will be obtained at steady state from the last 3 min of the 6MWT using a custom-written Matlab script (V.2019; MathWorks, Natick, Massachusetts, USA). From these outcomes, walking energy cost in J/kg/m will be calculated by using the following formula: ((4.940 x RER)+16.040)xVO_2_)/walking speed where VO_2_ is in mL/kg/min.^30^ The assessment of walking energy cost has previously been shown to be reliable in patients with NMD.^31 32^

The achievement of personal treatment goals will be quantified with the Goal Attainment Scale (GAS) to capture the diversity of orthotic treatment goals important to the individual patient.^33^ At baseline, two goals that are highly relevant to the individual will be determined with the patient based on what they wish to achieve in daily life in terms of activities and participation according to the International Classification of Functioning, Disability and Health (ICF) framework.^20^ Subsequently, personal GAS scales will be determined by creating six distinct levels of outcome ranging from −3 to +2, where the desired attainment goal of the patient is defined as 0 and the current situation is defined as −2. Achievement of the goals will be scored at T2 and T3 as −3=worsened, −2=unchanged, −1=somewhat less than expected, 0=expected outcome, +1 = somewhat more than expected and +2 = much more than expected. Improvements of at least two points will be regarded as clinical relevant.^34^ The investigator defining and scoring the GAS, followed a course in applying GAS within a rehabilitation context.^35^

#### Secondary outcomes

Secondary outcomes include walking speed (measured during the 6MWT), gait biomechanics (explained below), perceived stability during walking (assessed with a 11-point Numeric Rating Scale (NRS)), perceived physical functioning (PF) (assessed with the Short-Form Health Survey PF scale (SF36-PF),^36^ frequency of falls and fear of falling (assessed with the short version of the Falls Efficacy Scale (FES),^37^ perceived fatigue (assessed with the Fatigue Severity Scale (FSS)^38^ and satisfaction with the orthosis (assessed with the Dutch version of the Quebec User Evaluation of Satisfaction with Assistive Technology (D-QUEST)^39^ added with self-designed items).

#### Gait biomechanics

Gait biomechanics will be assessed with a 100 Hz 12-camera 3D motion capture system (VICON MX V.1.3) and two adjacent 1000 Hz force plates (OR6-7; AMTI, Watertown, Marssachusetts, USA). Preparations include placement of reflective markers on the body according to the Plug-In Gait model. After a static calibration, participants will be asked to walk along a 12 m long walkway. Conditions that will be assessed include barefoot walking (T1), walking with the current orthosis if applicable (T1) and walking with the new orthosis (T2 and T3). Per condition, at least three valid trials will be used for analysis containing a clear stance phase on the force plate for both feet and full visibility of all markers during the gait cycle. Joint angles, net joint moments and joint powers around the hip, knee and ankle will be calculated per trial and averaged over three trials. Spatiotemporal gait parameters (such as step length and step width) and relevant kinematic and kinetic variables (such as maximal ankle dorsiflexion angle, peak ankle power, knee angle and knee moment at midstance, hip flexion angle and maximal hip, knee and ankle angle during swing and progression of the centre of pressure) will be obtained from these averaged data and used for analysis.

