### Study population

We intend to include 70 adults with slowly progressive NMD (such as Charcot-Marie-Tooth disease, postpolio syndrome, inclusion body myositis or myotonic dystrophy) or peripheral nerve injury who have non-spastic leg muscle weakness. For eligibility, patients may or may not use an orthosis provided in usual care at the time of recruitment. Patients will be recruited from rehabilitation centres and hospitals throughout the Netherlands and through the Dutch Association for Neuromuscular Diseases. If a patient is willing to participate, a screening visit is planned. During the screening visit, written informed consent (online supplemental file 2) is obtained and the investigator, in close collaboration with a rehabilitation physician, will check the inclusion and exclusion criteria.

10.1136/bmjopen-2020-039683.supp2Supplementary data

Inclusion criteria are: (1) minimum age of 18 years, (2) weakness of the calf muscles (ie, Medical Research Council (MRC) scale^29^ score <5 or not being able to make a heel-rise on one leg >3 times) and/or weakness of the quadriceps (ie, MRC score <5) (3) experiencing walking problems such as increased walking effort, pain and/or impaired balance during standing and/or walking, (4) able to walk for 6 min at comfortable speed with or without assistive device (eg, cane, crutch, walker), (5) indicated for an orthosis based on physical examination and 3D gait analysis and (6) motivated to use an orthosis. An exclusion criterion is: (1) insufficient mastery of the Dutch language.

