### Sample size

The sample size of this study is based on a power analysis of the expected differences in walking effort (defined as gross walking energy cost) and the achievement of personal treatment goals between the intervention and control group. According to previous studies,^16 17^ a difference in change in walking energy cost of 0.60 J/kg/m from baseline to 6 months post-treatment is expected between usual orthotic care and specialised orthotic care, where a difference of at least 0.45 J/kg/m is considered as clinical relevant.^3^ Based on an intention-to-treat analysis, alpha of 0.05, power of 80% and using an estimated correlation coefficient of the repeated measures of 0.76 and SD of 0.90 J/kg/m, 30 patients per treatment group are necessary. The goal is to include 70 patients allowing for a 15% drop-out. This sample size also allows the detection of 1 point difference in personal achievement goal scores (Based on an intention-to-treat analysis, alpha of 0.05, power of 80%, and using an estimated correlation coefficient of the repeated measures of 0.70).

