### Randomisation and blinding

After baseline measurement (T1), participants will be randomly assigned in a 1:1 ratio to receive specialised orthotic care (intervention group) or usual orthotic care (control group). The randomisation scheme will be computer generated in Castor (Castor EDC, Amsterdam, the Netherlands) and uses blocks of random sequences with variable sizes (2, 4 and 6). Patients will be stratified by disease severity defined as distal leg weakness versus (distal and) proximal leg weakness, respectively. Outcomes will be assessed by a blinded and independent assessor. When patients are informed of group allocation, they will be instructed not to reveal this to the outcome assessor.

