### Statistical analysis

Walking energy cost and secondary outcomes at each measurement point (T1, T2 and T3) will be analysed with linear mixed models for repeated measurements to investigate the effectiveness of specialised orthotic care compared with usual orthotic care over time, adjusted for stratification and differences in baseline scores. Time and study group will be included as dependent variables. The differences in GAS scores between groups at 3 and 6 months follow-up will be tested with non-parametric Mann-Whitney U tests, as GAS scores are ordinal. All comparisons between groups are based on an intention-to-treat analysis.

For the economic evaluation, mean differences in total costs and effects between groups will be estimated using seemingly unrelated regression analyses. To account for the skewed nature of cost data, 95% CIs surrounding cost differences will be estimated using bias corrected and accelerated bootstrapping with 5000 replication. Subsequently, incremental cost-effectiveness ratios will be calculated by dividing the mean differences in costs by the mean differences in effects. To illustrate the joint uncertainty surrounding costs and effects, cost-effectiveness planes and cost-effectiveness acceptability curves will be plotted. In a cost-effectiveness acceptability curve, the probability of specialised orthotic care being cost-effective compared with usual orthotic care is plotted for a range of willingness to pay values (ie, the amount of money decision-makers are willing to pay per unit of effect gained).

All statistical analyses will be performed using SPSS (V.25; IBM SPSS) and a statistical significance of p<0.05 will be used in this study.

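### Table 1 and the gait section disagree on the baseline gait condition for patients without an orthosis: shoes-only walking is to be analysed but is not listed for measurement at T1

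*Protocol article*

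**What the plan says.** The Gait biomechanics section assigns walking conditions to visits. At T1: "Conditions that will be assessed include barefoot walking (T1), walking with the current orthosis if applicable (T1"). At follow-up: "walking with the new orthosis (T2 and T3"). It requires at least three valid trials for each condition.

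The footnote attached to the gait analysis row of Table 1 defines what is analysed: "Gait analysis conditions at baseline that will be used for statistical analysis concern walking with shoes only or walking with the old orthosis", the latter for participants who use an orthosis at baseline.

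Both kinds of patient are enrolled. Under Study population, "patients may or may not use an orthosis provided in usual care at the time of recruitment". The share of users is not given. Under Usual orthotic care, control patients who already have an orthosis receive a new one, which may be the same as the old one or different.

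Under Statistical analysis, "Walking energy cost and secondary outcomes at each measurement point (T1, T2 and T3) will be analysed with linear mixed models", and these models are "adjusted for stratification and differences in baseline scores". The stratification factor is given under Randomisation and blinding: "Patients will be stratified by disease severity defined as distal leg weakness versus (distal and) proximal leg weakness". Baseline orthosis use is neither a stratum nor a named covariate.

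**The concern.** For a patient without an orthosis, the only T1 gait condition the methods name (barefoot) is one the analysis does not use, and the only one the analysis uses (shoes only) is one the methods do not name. A measurement team working from the gait section alone would not record the planned baseline for any of these patients. A T1 condition that was not recorded cannot be recovered as a baseline once the new orthosis is in use. If barefoot data were substituted, the baseline would be unshod and the follow-up would be walking with the new orthosis, so the change would mix the effect of shoes with that of the device.

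A second, lesser matter follows from the Table 1 definition itself. The gait baseline is a no-device measurement for some patients and an old-device measurement for others. A single baseline slope treats the two as the same quantity, although change means the effect of a first device in one subgroup and of a replacement in the other. This can weaken the baseline score as a predictor of follow-up and so cost some precision.

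**Working it through.** **1. The two places side by side (T1 gait analysis)**

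| Patient at baseline | Measured, per Gait biomechanics | Analysed, per Table 1 footnote |
|---|---|---|
| Uses an orthosis | Barefoot; current orthosis | Old orthosis |
| Does not use one | Barefoot | Shoes only |

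For users the two agree: the analysed condition is among those measured. For non-users they do not, and shoes-only walking appears in the article only in the footnote.

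**2. The plan's own sample size, to see whether it is touched**

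Inputs from Sample size: difference 0.60 J/kg/m ("a difference in change in walking energy cost of 0.60 J/kg/m from baseline to 6 months post-treatment is expected"), SD 0.90, alpha 0.05 (taken as two-sided), power 80%, correlation 0.76, drop-out 15%.

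- Unadjusted: n = 2 × [0.90 × (1.960 + 0.842) / 0.60]² = 35.3 per group.
- With the repeated-measures factor for three measurements, (1 + 2 × 0.76)/3 = 0.84: 35.3 × 0.84 = 29.7, so 30 per group, as stated.
- Drop-out: 60/0.85 = 70.6, against the stated 70, which is within rounding.

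The figure concerns walking energy cost and does not depend on the gait baseline.

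**3. Precision available from a term for baseline orthosis use**

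The documents give neither the user share p nor the size d of the shift an old orthosis causes at baseline, so both are assumed. The model is ANCOVA-type: true baseline-to-follow-up correlation r = 0.76, and a shift at baseline only. The SD of 0.90 and the correlation are the energy-cost values. The article gives none for the gait variables, so for those the results are an illustration in SD units.

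With s = d/0.90, ignoring use lowers the squared correlation to r²/(1 + p(1−p)s²). With p = 0.5 and r² = 0.5776, this is 0.5776/(1 + 0.25s²). The residual fraction with use in the model is 1 − 0.5776 = 0.4224.

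| d (J/kg/m) | s | r² ignoring use | Residual ignoring use | Share removable |
|---|---|---|---|---|
| 0 | 0 | 0.578 | 0.422 | 0% |
| 0.25 | 0.28 | 0.567 | 0.433 | (0.433 − 0.422)/0.433 ≈ 2.5% |
| 0.50 | 0.56 | 0.536 | 0.464 | (0.464 − 0.422)/0.464 ≈ 9% |
| 0.75 | 0.83 | 0.492 | 0.508 | (0.508 − 0.422)/0.508 ≈ 17% |

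Over a wider range (users 30% to 70%, shift 0.5 to 1.0 SD), the usable correlation falls to between 0.68 and 0.74, and ignoring use raises residual variance by about 7% to 27%.

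**The case against.** The best defence of the gait section is that its list says the conditions include those named, so it may be open-ended, and that Table 1 does fix the analysed baseline. A reader might infer that the shoes-only baseline will in fact be missing. The article does not show that; the trials may be recorded without being listed. What survives is that a visit-by-visit list naming an unanalysed condition and omitting the analysed one needs correcting, even if open-ended. Condensation does not explain it either, because both statements stand in the same article.

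On the model term the opposing case is stronger. Adjustment for stratification and baseline score is conventional, enrolling users and non-users together is a deliberate choice, and further covariates may sit in an analysis plan not shown. A reader might infer that leaving out orthosis use biases the group comparison. It does not: randomisation balances use between groups in expectation, leaving only precision and chance imbalance.

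A reader might also take the gain to be larger, by setting 0.25d² (0.016, 0.063, 0.141) against the baseline-adjusted residual variance 0.81 × (1 − 0.76²) = 0.342, which gives 5%, 18% and 41%. That sets a difference in mean change against a residual already adjusted for baseline. When the shift arises at baseline, the baseline score absorbs part of it, and the figures are roughly halved.

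Finally, the footnote applies only to gait analysis. The Primary outcomes section does not say whether the baseline 6-minute walk is done with the old orthosis, so extending the point to walking energy cost is conditional.

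**Conclusion.** The contradiction stands and should be corrected. It affects the baseline of the gait secondary outcomes for every patient without an orthosis, a share the article does not state. It does not affect the sample size, and nothing in the article shows that it reaches either primary outcome.

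The absence of a term for baseline orthosis use is neither an error nor a source of bias. Adding it is an inexpensive gain in precision: about 2.5%, 9% or 17% of residual variance under the assumed half share of users and baseline-only shifts of 0.25, 0.50 or 0.75 J/kg/m, and nothing if there is no shift. These figures rest on the assumed share and shift, and on the energy-cost SD and correlation standing in for those of the gait variables.

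**What to change.** - **Reconcile the two places.** In Gait biomechanics, list shoes-only walking as a T1 condition for patients without an orthosis, matching the Table 1 footnote, and keep barefoot walking as descriptive. Cost: one sentence, plus a few walking trials per such patient if shoes-only is not already recorded.
- **Recommended, for precision.** Add baseline orthosis use (yes/no) as a main effect in the gait models. It is already known at T1, because Table 1 has satisfaction and orthotic properties assessed at baseline only in users. Cost: one parameter per model.
- **Conditional.** State whether users wear the old orthosis in the baseline 6-minute walk. If they do, add the same main effect to the walking energy cost model.
- **Optional.** An interaction of orthosis use with baseline score may be considered, but the article does not establish a need for it.

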#### Economic evaluation

The economic evaluation will be performed from a societal and a healthcare perspective. When the societal perspective is applied intervention costs (costs directly related to the delivery of the orthosis) healthcare costs (costs related to visits to general practitioners, medical specialists, and/or therapists, medication use and assistive devices) informal care costs, unpaid productivity costs, as well as costs related to productivity losses due to being absent from work (absenteeism) and productivity losses due to reduced productivity while being at work (presenteeism) will be included and assessed with a cost questionnaire. When the healthcare perspective is applied, only costs accruing to the formal Dutch healthcare system will be included. To collect data on resource use, participants are asked to fill in cost questionnaires at baseline (T1), directly after delivery of the orthosis and at 3 and 6 months post orthotic treatment (T2 and T3). All cost categories will be valued in accordance with the Dutch manual for costing studies in healthcare.^40^

Outcome measures used for the economic evaluation will be quality-adjusted life years (QALYs), walking energy cost and GAS scores. QALYs will be based on the 5-Level version of EuroQol 5 Dimension (EQ-5D-5L), administered at each measurement point (T1, T2 and T3). The patients’ EQ-5D-5L health states will be converted into utility scores using the Dutch tariff.^41^ Subsequently, QALYs will be estimated by multiplying the patients’ utility scores by the time spent in a certain health state.

